### Annual safety report

An annual report concerning the safety of the subjects, consisting of a complete safety analysis will be submitted to the MEC.

**Follow-up of adverse events**

All adverse events will be followed until they have abated, or until a stable situation has been reached. Depending on the event, additional tests or medical procedures and/or referral to a medical specialist will be performed accordingly.

**Alcohol administration**

Before starting each experiment, the subjects will be fully examined and routine biochemical analysis including liver function tests will be performed. Preparations of ethanol and sugar solutions will be performed in a food grade kitchen at Maastricht University ([name]). The solution will be prepared from pure food grade ethanol diluted in tap water up to 200ml (final concentration of 10%).

The subject will not be allowed to leave the hospital before their exhaled breath test levels are within the normal and safe limits.

**Blood sampling**

During blood sampling, the subjects will remain seated in a comfortable chair, with an adjustable back. No side effects are expected when sampling blood in this manner43.

**Gut permeability test**

All ingredients of the test beverage (lactulose, L-rhamnose) are used in food industry and are generally regarded as safe. No health risks are associated with the consumption of the test beverage and the subsequent collection of blood. Furthermore, the application of Lactulose and L-rhamnose which will be used has been approved previously by this Medical Ethics Committee (MEC 08-2-070, MEC 04-168).

**Gastroduodenoscopy**

The gastroduodenoscopy, performed by a gastroenterologist, is a standard procedure that takes 10 to 20 minutes. During the procedure 8 biopsies will be taken with a standard biopsy forceps. Diagnostic upper GI endoscopy is a remarkably safe procedure. Although there are no recent high quality prospective studies of complications following diagnostic upper GI endoscopy, one large US study estimated an overall complication rate (including mucosal biopsy) of 0.13% and an associated mortality of 0.004% 44. Perforation related to diagnostic upper GI endoscopy is uncommon with an estimated frequency of 0.03 and mortality of 0.001% 44.

**Alcohol concentration determination by exhaled breath**

The exhaled breath test is a simple and non invasive technique used for measurement of blood alcohol concentration. It’s also used in roadside studies on the effects of alcohol on driving performance. The subjects will stay at the motility room located at MUMC under supervision and will not be allowed to leave MUMC unless their blood alcohol concentrations are within the legal limit 0.05 g/dl (0.05 % w/v)45.

**Ethics**

The study will be conducted according to the principles of the Declaration of Helsinki and in accordance with the Medical Research Involving Human Subjects Act (WMO). Participants will be informed about the study by the principal investigator by both by written information and personal communication.

A time period of one week will be provided to decide whether they would like to participate. All participants will have to sign an informed consent. Participants can at any time make an appeal to the independent doctor, dr. [name] ([contact]) who has agreed to be the independent doctor for this study. Participants will be informed that their decision to participate is totally voluntary and they can withdraw at any time without giving a reason. ~~This will not influence further treatment by their physician.~~ Participants will have the opportunity to be informed about their individual results and the group results at the end of the study.

**Methodological aspects**

**Samples size**

Previous work ([name] et al) showed increased small intestinal permeability using indomethacin as stress model. The small intestinal permeability was assessed by the lactulose / rhamnose ratio. The lactulose / rhamnose ratio increased from 0.013±0.009 at the base line to 0.031±0.020 after indomethacin treatment.

According to these data the SD in indomethacin-treated group would be 0.020 and the difference in the mean was 0.018. Considering this difference and using a SD of 0.02, twelve subjects (n=12) are required.

Sample size was determined using the following power calculation program:

[http://biostat.mc.vanderbilt.edu/twiki/bin/view/Main/PowerSampleSize](https://webmail.unimaas.nl/exchweb/bin/redir.asp?URL=http://biostat.mc.vanderbilt.edu/twiki/bin/view/Main/PowerSampleSize) , Version 3.0.

 = 0.05, power = 80%.

**Data analyses**

The dependent variables will be analyzed with the Wilcoxon signed-ranked test, when the distribution of the variables is non-parametric. If the variables are normally distributed a paired t-test will be done.

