**The definitive study**

The definitive study will be executed according to a double-blind, placebo-controlled randomized, crossover trial.

The subjects will undergo two study days in a random order, namely ethanol intervention with permeability tests or placebo intervention with permeability tests, with a one week wash out period in between.

**
[figure not shown]
**

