**General considerations**

All subjects participating will be requested to refrain from heavy physical exercises. Consumption of alcoholic beverages will be prohibited during one week prior to each study day. In order to standardize food intake among different individuals, three days prior to each day of the study, standard meals will be provided.

The subjects will be fasting overnight from 22:00 h the night before to 08:00 h in the morning each study day. During the study day, subjects will be allowed only to drink water or tea without sugar. Once all tests are performed, a meal will be provided and a hospital bed will be present to rest when necessary. Before the subjects can leave the hospital, ethanol levels will be determined by exhaled breath test. The exhaled breath test will be performed to determine the legal limit of blood alcohol (BAC) concentration 0.05 g/dl (0.05%). Subject will stay at the motility room located at Maastricht University Medical Center (MUMC), under supervision. Transportation home will be provided (taxi).

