**Duodenal biopsy specimen**

Tissue samples from the horizontal part of the duodenum will be obtained by standard flexible gastroduodenoscope at the endoscopy unit of Maastricht University Medical Center (MUMC) and will be performed by an experienced gastroenterologist. The procedure is widely used in medical practice. Its application in human intervention trials was approved previously by this Medical Ethical Committee (MEC 01-149, MEC 03-196, MEC 05-118). Briefly, in the seated position, an anaesthetizing spray (Xylocaine 2%, Astra Pharmaceutica BV, Zoetermeer, The Netherlands) will be sprayed in the throat to locally anaesthetize the pharynx. A plastic ringlet will be placed in the mouth. The gastroscope will be inserted through the mouth, the oesophagus and the stomach, and into the proximal duodenum, respectively. Eight biopsies of approximately 5 mg of the epithelial tissue will be taken using small (standard) forceps. Upon obtaining the biopsies, the gastroscope will be retracted. The air in the stomach will be aspirated before removing the endoscope. The intestinal mucosa heals quickly from such biopsies.

The biopsy specimens will be used to determine the following:

- Mucosal ethanol and acetaldehyde concentrations.
- Tight junction functionality by
  - Transmission electron microscopy to study the morphological changes of TJs in response to ethanol.
  - Immunofluorescent labelling of perijunctional actin, myosin, ZO-1, myosin light chain kinase, and phosphorylated myosin light chain.
  - *Ex vivo* determination of the effects of ethanol and acetaldehyde on tight junction functionality using Ussing chambers.
- Expression of different genes involved in the regulation of the TJs proteins, ethanol metabolism and the inflammatory cytokines.

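### The randomised two-period crossover is analysed with paired tests that ignore period; this costs power if the two study days differ, and biases the estimate if the sequences also end up unequal

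*Protocol*

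**What the plan says.** The definitive study section describes a "double-blind, placebo-controlled randomized, crossover trial". On order and spacing it says "The subjects will undergo two study days in a random order", "with a one week wash out period in between". It does not say how sequences are allocated or whether the two will be equal in size.

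Data analyses is two sentences long. "The dependent variables will be analyzed with the Wilcoxon signed-ranked test" when the distribution is not normal; otherwise, "If the variables are normally distributed a paired t-test will be done". No term for period or sequence appears.

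Samples size plans 12 subjects for 80% power at alpha 0.05, from earlier indomethacin data in which "the difference in the mean was 0.018" and the SD was taken as 0.02.

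**The concern.** In a two-period crossover, any general difference between the first and second study day enters the ethanol-minus-placebo difference with one sign in one sequence and the opposite sign in the other. A paired test does not know which sequence a subject was in. It therefore treats the day difference as random error, and if the sequences differ in size, part of that difference stays in the estimated ethanol effect. Sequence is known for every subject, so both consequences can be removed with information the trial already holds. With 12 subjects and planned power just above 80%, there is little room to absorb an avoidable loss.

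Two features of the schedule differ between the days. First, "Consumption of alcoholic beverages will be prohibited during one week prior to each study day", so volunteers have had about one week without their own drinking at the first day and about two at the second. Second, "Eight biopsies of approximately 5 mg of the epithelial tissue will be taken using small (standard) forceps" at endoscopy, so the second day follows a biopsy session a week earlier. These make a period effect conceivable; they do not show one.

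**Working it through.** **Inputs.** From Samples size: effect τ = 0.018, SD = 0.02, n = 12, alpha 0.05, power 80%, baseline ratio 0.013. From The definitive study: two sequences, two periods. Assumed: the period shift π (mean change from day 1 to day 2), because the protocol gives none. The values used are 0.0045, 0.009 and 0.012, which are 35%, 69% and 92% of the baseline ratio.

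**The plan's own figure.** Iterating n = [(t(n−1, 0.975) + t(n−1, 0.80)) × 0.02 / 0.018]² gives 11.74, rounded up to 12. Exact noncentral-t power at n = 12 is 81.0%. So 12 is reproduced as a two-sided paired t-test, provided 0.02 is read as the SD of the paired differences. The protocol takes it from the values after indomethacin. That reading is kept here.

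**Effect of a shift.** Let D be ethanol minus placebo.

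- Placebo first (n1 subjects): mean of D = τ + π
- Ethanol first (n2 subjects): mean of D = τ − π
- Bias of the paired mean = π(n1 − n2)/n
- Expected error variance in the paired test = 0.02² + π² × 4·n1·n2 / [n(n − 1)]

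**Balanced, 6:6.** The bias is zero. The error variance is 0.02² + π² × 144/132. The mean of D has true variance 0.02²/12, while the sum of squares is noncentral chi-square on 11 df with noncentrality 12π²/0.02². Integrating over that distribution gives:

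| π | Expected error SD | Paired-t power | Paired-t type I error | Adjusted power |
|---|---|---|---|---|
| 0 | 0.0200 | 81.0% | 5.0% | 80.2% |
| 0.0045 | 0.0205 | 79.4% | 4.5% | 80.2% |
| 0.009 | 0.0221 | 74.6% | 3.3% | 80.2% |
| 0.012 | 0.0236 | 69.5% | 2.4% | 80.2% |

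Simulation agrees with these powers to within about 0.2 percentage points. At π = 0.003 the paired test has 80.3%, so the two analyses break even at about that shift.

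**Period-adjusted test.** The estimate is the average of the two sequence means of D. Its standard error is (0.02/2) × √(1/n1 + 1/n2), on 10 df, and π drops out.

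- 6:6: SE = 0.01 × √(1/6 + 1/6) = 0.00577; power 80.2%
- 7:5: power 79.1%
- 8:4: SE = 0.01 × √(1/8 + 1/4) = 0.00612; power 75.5%

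**Unequal sequences, paired test.** At 8:4 the bias is π × 4/12 = π/3. For π = 0.009 that is 0.003, or 17% of the planned 0.018. If the imbalance works against ethanol, paired-t power falls to about 59%. If it works the other way, the effect is overstated.

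The Wilcoxon signed-rank branch has the same structure but was not quantified separately.

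**The case against.** Several points on the other side stand.

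- **No period effect is documented, and parts of the protocol argue against one.** A reader might infer that the schedule builds one in. The text does not support that. The biopsy section itself says the mucosa recovers quickly. The Introduction cites a study in which the permeability effect of a single high dose was gone within a day in healthy volunteers, and within four days in chronic alcoholics. The first study day already follows a full week without alcohol, and meals, fasting and exercise are handled alike before both days.
- **The larger shifts are severe.** Shifts of 0.009 and 0.012 are 69% and 92% of the baseline ratio. At 0.0045 the loss is under 2 points, and up to about 0.003 the paired test is no worse than the adjusted one.
- **A reader might infer that false positives are inflated or that the primary estimate is biased as planned.** At 6:6 neither is so: the estimate is unbiased and the test conservative. Bias needs both a shift and a realised imbalance. Averaged over simple randomisation, type I error stays at 5.0% to 5.2% for shifts of 0.009 and 0.018.
- **The allocation scheme is unstated, not stated badly.** Under simple randomisation a split of 8:4 or worse would occur in 39% of trials, but the protocol does not say randomisation is simple. Silence on list details is not a fault in itself.

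It can also be said that model terms belong in a statistical analysis plan. That carries less weight here: the protocol names the tests, so a plan that follows it inherits the omission.

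**Conclusion.** The point holds as an inexpensive improvement to the analysis, not as an error that invalidates the trial. The named tests discard the order that was randomised. If the two days differ by 0.0045, 0.009 or 0.012 in the ratio, a balanced trial loses about 1.6, 6.4 or 11.5 points of power (81.0% minus 79.4%, 74.6% and 69.5%), without bias. If the sequences are also unequal, the estimate carries a bias of π(n1 − n2)/n.

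This rests on an SD of 0.02 for the paired differences within sequence, an effect of 0.018, normal data, and shifts that are assumptions. The sample size of 12 is not shown to be wrong: it reproduces on its own inputs and still meets 80% under the adjusted analysis at 6:6.

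**What to change.** Make two changes together, before unblinding.

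1. State that sequences are allocated 6:6 from one permuted list.
2. Analyse the primary outcome with a linear model containing subject, period and treatment. Equivalently, compare the period-1 minus period-2 differences between the two sequences, with a rank-sum test on those differences as the non-parametric version. The same model can serve the secondary outcomes measured on both days.

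The cost is wording and one degree of freedom: with no period shift, power goes from 81.0% to 80.2% at 6:6. Adjustment without balance is dearer, at about 75.5% for 8:4. Balance without adjustment removes the bias but leaves the power loss. Adding period after the data have been seen would be a data-driven change to the primary analysis, so it should be settled beforehand.

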**Insurance**

Insurance for the participants will be provided in accordance with the legal requirements in the Netherlands (Article 7 WMO and the Measure regarding Compulsory Insurance for Clinical Research in Humans of 23rd June 2003). Maastricht University Medical Centre has got a standard WMO-insurance and liability insurance for research participants.

**Administrative aspects and publication**

**Handling and storage of data**

Data are handled confidentially and coded. The privacy of the participants is guaranteed. All samples and data will be coded in such a way that no personal information about the participants will be available. The key of the code will be kept by the principal investigator, to which only the principal investigator has access. All primary documents and data will be kept for 15 years after the end of the experimental phase of the study for possible inspection. Samples taken from the participants during the study will be kept for 4 years after the end of the experimental phase of the study for additional analysis on epithelial integrity or inflammation.

For future analyses of the study materials, the subjects will not be asked for permission the analyses are within the scope of the present study, Nevertheless, the MEC will be asked for permission to perform these analyses in case the future analyses are not within the scope of the present study.

**Amendments**

All substantial amendments will be notified to the METC that gave a favourable opinion.

**Report progress and end of study**

The investigator will submit a summary of the progress of the trial to the accredited METC once a year. Information will be provided on the date of inclusion of the first subject, numbers of subjects included and numbers of subjects that have completed the trial, serious adverse events/ serious adverse reactions, other problems and amendments.

The investigator will notify the accredited METC of the end of the study within a period of 8 weeks. The end of the study is defined as the last participant’s last visit. In case the study is ended prematurely, the investigator will notify the accredited METC, including the reasons for the premature termination. Within one year after the end of the study, the investigator/sponsor will submit a final report with the results of the study including any publications/abstracts of the study to the accredited METC.

**Publication policy**

All trial results, both positive and negative will be disclosed in agreement with the CCMO statement on publication policy.

Based on the results of this study, at least one publication will be submitted for publication to a peer-reviewed scientific journal. The authorship of the article will be determined in appropriate consultations based on a considerable contribution to the set-up and execution of the study and an active participation in publication. The financial contributor (Top Institute Food and Nutrition) is entitled to examine the manuscript prior to publication and to make comments on it. Within two weeks of the receipt of the draft article Top Institute Food and Nutrition will inform the parties involved whether it wishes for a deferment, to offer Top Institute Food and Nutrition an opportunity to protect its (commercial) interests and rights. Any such deferral will be of a maximum of two months. None of the parties concerned has the right of veto considering publication.

